**Hypothesis:**

1. Physicians with individualized access to their energy levels, oxygen level, respiratory rate, stress levels, sleep patterns, and heart rate will engage more frequently in behaviors that mitigate stress, resulting in improved well-being.
2. Fatigue, stress, and overall quality of life will improve while burnout will be less impacted by wearing a Smartwatch.
3. Physiologic parameters, collected from Smartwatches, will relate to physician's subsequent endorsement of symptoms of fatigue, stress level, and overall quality of life more closely than their measured symptoms of professional burnout.

In this study, physicians will be asked to wear a Smartwatch and answer a survey at baseline, 3-, 6-, 9-, and 12-months. We will determine if physicians who wear a Smartwatch and have access to its data experience greater improvements in their well-being relative to physicians not wearing a Smartwatch (control group). In addition, we will collect data from the Smartwatches to determine if we can utilize this data to predict subsequent level of well-being. We will build the

infrastructure and a HIPAA compliant de-identified dataset which includes (i) continuous physiology measures (from Smartwatches; raw data gathered for every 15-second epoch) and (ii) survey responses. We will use this dataset to develop predictive models for well-being derived from physiologic measures. Prediction models established using the cohort in Arm 1 will be validated in the cohort in Arm 2 after they cross-over (at the 6-month time-point) and begin using the Smartwatch.

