Despite these recommendations from the National Academy of Medicine, few intervention studies have been conducted to-date involving residents and physicians to guide personal and organizational strategies. In previous randomized controlled studies, funded by the Physicians Foundation, we demonstrated that professional coaching reduced overall burnout and improved quality of life and resilience among physicians. It remains unknown, however, if physicians at risk for burnout or poor well-being in other dimensions will recognize it and proactively take steps to engage in professional coaching.

In this proposed study, we plan to conduct a 2-arm randomized controlled trial evaluating the effectiveness of 6 months of wearing a Smartwatch and having access to one's physiologic data to improve well-being among physicians. There is increased ubiquity of wearable technologies such as Smartwatches, that provide quantitative measures of one's physiological functioning (e.g., heartrate, sleep cycles, sleep quality) that may serve as a real-time surveillance mechanism to

forecast impending burnout or changes in other dimensions in well-being, potentially triggering individual intervention before suffering or negative impact to patient care occurs. We anticipate that providing physicians with individualized access to their energy levels, oxygen level, respiratory rate, stress levels, sleep patterns, and heart rate will promote behaviors that mitigate stress, resulting in improved well-being.

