Once we have recruited the appropriate number of physicians, we will administer the baseline survey. After completion of the baseline survey, Consented physicians will be randomly assigned via computer-generated algorithm to one of two groups: Arm 1 = Smartwatch Intervention; Arm 2 = Control. Randomization will be stratified by gender, specialty, work site, and physician category (resident or physician in-practice) using permuted blocks.

Participants randomized to the Smartwatch Intervention arm will receive a Garmin Smartwatch after enrollment and completion of the baseline survey. Garmin Smartwatches are sleek and provide the broadest range of all-day health monitoring features to keep track of energy levels, pulse oximetry, respiratory rate, stress levels, sleep patterns, and heart rate while operating with 18-hour battery life per charge cycle. Participants will be asked to wear the Garmin watch much as possible during the 12-month study period.

Participants randomized to the Control arm will receive no intervention for the first six months of the study, at which point they will receive Garmin Smartwatches after completion of the 6 month survey.

**Smartwatch Issuance.** Study subjects will be issued a Garmin Venu 2 Plus or Venu 3s smartwatch (control group subjects will receive the Venu 3s model). For these procedures, trained research staff will de-identify subjects (subject ID and anonymized number ID maintained by PIs) and enroll them into Garmin Connect (for collecting data from Garmin smartwatches) and Fitabase. The study coordinator will work with each subject to identify the best way (time and place) to deliver their smartwatch. At the time of delivery, subjects will also receive a printed manual with step-by-step instructions for setting up linkages with Garmin and Fitabase. Prior to delivery, each subject will also receive an individualized email with a unique link needed for setting up the Fitabase data extractor.

Research staff will train subjects on the use and basic maintenance of the smartwatches. Subjects will be informed that research staff can be contacted any time questions arise about the basic operation and maintenance of the smartwatches. Contact information for research staff will be provided.

Study team will promote engagement through bi-weekly in person visits or email as a way to remind regular synchronization of their watch data or completion of quarterly surveys.

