The surveys will include the validated Well-Being Index, Maslach Burnout Inventory, Linear Analogue Self-Assessment quality of life scale, Perceived Stress Scale, and Epworth Sleepiness Scale, and Quick Inventory of Depressive Symptoms (QIDS-SR). No instrument or question in this survey is designed to diagnose depression or screen for major depressive disorder or suicidality. Each of these metrics has been validated across a wide range of medical conditions and populations, including physicians. Additional self-reported items will explore workplace factors (e.g., work hours, call frequency, shift work, work location [inpatient, outpatient, surgical], etc.), self-reported medical error, and use of organizational provided stress management and fatigue mitigation strategies. Items can be found in the Survey Instrument document. As a token of appreciation, participants will receive \$25 for each survey completed.

Finally, smartwatch data (energy levels, respiratory rate, stress levels, sleep patterns, and heart rate) will be collected via FitaBase - a 3rd party data aggregator which will not collect any PHI. We have already tested and developed a parser to query Garmin's system every 14-days, download the raw data, and process them for analyses by summarizing the sensor features by the minute, hour, day, week or month and store into REDCap database.

During the final quarter of the study, March 1-May 31,2024 participants who wear their watches for an average of 70% of the time will receive a \$25 e-gift card. This purpose of this incentive is to maximize data to enhance analysis. The data analytic methods rely on complete data for meaningful predictions and can only handle data missingness up to 30%. The wear time goal reflects the threshold needed for data analysis. Wear time will be measured by the watch based on detected heart rate. Participants will be notified of the incentive through the regular newsletter.

During the final quarter of the study, March 1-May 31,2024 participants who wear their watches for an average of 70% of the time will receive a \$25 e-gift card. This purpose of this incentive is to

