#### **F. Data Analysis Plan:**

For Aim 1, we will compare changes in outcome variables between Arm 1 (Smartwatch Intervention) and Arm 2 (Control group) at 6 months. Then, we will explore the durability of the benefits of having a Smartwatch for 12 months, by examining levels of well-being among Arm 1 participants at the 6- and 12-month mark. We will use generalized estimating equations to account for the repeated-measures design. Tests will be 2-sided, and we will use the intent-to-treat principle in analyses.

To determine whether continuous physiological measures (measured from Smartwatches) contain a 'signal' that predicts physician well-being, and if so in which dimensions. We will construct Probabilistic Graph Models (PGMs) for low overall well-being (score  $\geq 2$ ), burnout (score of  $\geq 27$  on emotional exhaustion scale or score of  $\geq 10$  on the depersonalization score), low quality of life ( $\geq \frac{1}{2}$  SD below the mean), high stress (score  $\geq 17$ ), and high fatigue (score  $\geq 11$ ). We will derive dynamics for these dimensions of well-being using dynamic Bayesian networks (DBN). Data from Arm 1 will be used to train MTL models to predict risk of low well-being, burnout, low QOL, high stress, and high fatigue in the next quarter. Models will be tested and retrained using data from subsequent assessments. We will then evaluate the predictions using data from Arm 2 (control). Standard metrics of model performance (e.g., AUC, sensitivity, specificity) will be reported. Predictor variables will be ranked by the relative importance in making predictions, and the top 10 predictors (a heuristic for simplicity in deriving easily interpretable predictions in English sentences) will comprise Core Well-being Factors. We aim to achieve predictive accuracies > 70%.

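### Arm 1 models are retrained before they are scored in Arm 2, with no rule on which version is used, so on the natural reading the validation covers new people but no new period

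*Protocol*

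**What the plan says.** Section IV.F sets out the modelling in three steps. First: "Data from Arm 1 will be used to train MTL models to predict risk of low well-being, burnout, low QOL, high stress, and high fatigue", each for the quarter that follows. Second: "Models will be tested and retrained using data from subsequent assessments". Third: "We will then evaluate the predictions using data from Arm 2 (control").

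The Hypothesis part of section I says that models established in Arm 1 "will be validated in the cohort in Arm 2 after they cross-over (at the 6-month time-point) and begin using the Smartwatch". Section IV.C asks Arm 1 to wear the watch throughout: "Participants will be asked to wear the Garmin watch much as possible during the 12-month study period". Arm 2 receives its watches after the 6-month survey.

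Two statements in section IV.C put the arms on a common clock. Baseline waits for recruitment to finish: "Once we have recruited the appropriate number of physicians, we will administer the baseline survey". The wear-time incentive names one closing window without separating the arms: "During the final quarter of the study, March 1-May 31,2024 participants who wear their watches for an average of 70% of the time" qualify.

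Section II gives the purpose: the watch data may serve to "forecast impending burnout or changes in other dimensions in well-being".

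**The concern.** A forecast for a given quarter can only come from a model fitted before that quarter's outcomes are known. If the Arm 1 models are first updated with every later Arm 1 assessment and then scored in Arm 2, the scored model has seen outcomes from the same quarters in colleagues at the same two institutions. Anything that moves well-being for everyone in a quarter, such as season, workload surges or the academic year, can be learned from Arm 1 and credited in Arm 2 as predictive performance. A prospective user of the model would not have that information.

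At stake is how the Arm 2 accuracy, sensitivity and specificity can be read, and with them the protocol's aim of accuracy above 70%.

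**Working it through.** **Timeline.** Surveys fall at baseline and at 3, 6, 9 and 12 months in both arms (section IV.C).

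| Assessment | Arm 1 outcome with watch data | Arm 2 outcome with watch data |
|---|---|---|
| Month 3 | yes | no |
| Month 6 | yes | no |
| Month 9 | yes | yes |
| Month 12 | yes | yes |

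Arm 2 can be scored only at months 9 and 12. If retraining uses every later Arm 1 assessment, both of those quarters are already in the training data, from other participants. Nothing in the protocol freezes a version before month 6 or before month 9.

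**No figure of the plan to reproduce.** The 70% target is stated without a derivation. For a plausible size per arm: 184 × 0.85 = 156.4, or about 78 per arm if allocation is 1:1 (the ratio is not stated).

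**Size, by simulation.** All settings here are assumptions: 78 per arm; four quarters; one watch feature per quarter with log-odds slope 1.0 and intercept -0.4; a random person effect; a quarter effect on the logit scale common to both arms; 1,500 replicates. Arm 2 outcomes at months 9 and 12 were scored with a forward model (Arm 1 outcomes from earlier assessments only) and with a model retrained on all four Arm 1 quarters.

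| SD of shared quarter effect | SD of slope drift | Accuracy, forward | Accuracy, retrained | Difference | Within-quarter AUC, forward / retrained |
|---|---|---|---|---|---|
| 0 | 0 | 0.669 | 0.669 | 0 | 0.724 / 0.724 |
| 0.25 | 0 | 0.663 | 0.668 | 0.005 | 0.721 / 0.721 |
| 0.5 | 0 | 0.654 | 0.667 | 0.013 | 0.722 / 0.722 |
| 1.0 | 0 | 0.627 | 0.667 | 0.040 | 0.725 / 0.725 |
| 0.5 | 0.25 | 0.653 | 0.669 | 0.016 | 0.722 / 0.722 |
| 1.0 | 0.5 | 0.617 | 0.661 | 0.044 | 0.708 / 0.711 |

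The pattern is as expected. A shift in level changes how many people fall above a cut-off, but not their ranking within a quarter.

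**Pooled AUC.** If AUC is computed over both Arm 2 quarters together, a shift can enter it. Take the extreme case of a score that identifies the quarter exactly and carries no person-level information, with equal numbers per quarter and prevalences p1 and p2:

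AUC = 0.5 + 0.5 × [p2/(p1 + p2) − (1 − p2)/(2 − p1 − p2)]

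- 40% and 45%: 0.5 + 0.5 × (0.529 − 0.478) = 0.526
- 40% and 50%: 0.5 + 0.5 × (0.556 − 0.455) = 0.551
- 35% and 50%: 0.5 + 0.5 × (0.588 − 0.435) = 0.577

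These prevalences are assumed, and the values are upper bounds for their case.

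**A richer model.** A further simulation used 10 to 30 features, a penalised logistic model, shared shifts of 0.3-0.5 SD in the features and 0.3 SD in well-being, and 300 data sets per setting. With a moderate signal it gave accuracy of 61-63% retrained against 58-61% forward, and AUC of 0.64-0.67 against 0.61-0.65. About 0.01 of the AUC gap came from the smaller training set.

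**The case against.** **This is detail for the SAP.** Version control for a machine-learning aim often sits there, and the SAP is not at hand. It may set a freeze. The protocol also does not state outright that Arm 1's 9- and 12-month outcomes enter the model before the matching Arm 2 quarter is scored; section IV.C speaks only of development as data accumulate. This stands as a limit on certainty. But section IV.F itself fixes the order, retraining first and Arm 2 afterwards, so the point concerns a stated procedure.

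**The plan has a forward element.** The sentence on retraining also provides for testing on later assessments. Done before each update, that is a forward check. This stands, but it is a check within Arm 1, in the people who supplied the training data.

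**Arm 2 answers a legitimate question.** Aim 2 asks whether the physiology carries a signal. Testing in different randomized participants, with an outcome in the next quarter, is a fair test of that. This stands too. The limitation applies to the forecasting claim.

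**The effect is small against noise.** With 2 × 78 = 156 Arm 2 observations, the standard error of an accuracy of 0.667 is √(0.667 × 0.333/156) = 0.038, before allowing for correlation within persons. Even a 4-point difference is about one standard error. That is true of one estimate, but both versions would be scored on the same people, so much of this noise is shared when they are compared.

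**Stronger readings.** A reader might infer that the Arm 2 figures will overstate performance. The documents do not support that: it needs a shared shift, and none is quantified. A reader might infer that the 70% target would be met falsely. In the table above the retrained model stays between 0.661 and 0.669. A reader might also infer that classification cut-offs are tuned to the quarter's prevalence. The cut-offs in section IV.F define the outcomes, and no such tuning is described.

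**Conclusion.** The point holds as a limitation that is cheap to remove. The order of steps, the overlap of the arms in months 6-12 and the lack of a rule on the scored version all follow from the protocol. On the natural reading, Arm 2 tests transfer to new people but not to a new period, and may be optimistic as a test of next-quarter forecasting.

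The size ranges from nil, with no shared calendar shift, to about 4 points of accuracy at the largest shifts simulated. Sensitivity and specificity at a cut-off, and AUC pooled over quarters, are exposed in the same way. AUC within a quarter is hardly affected. These sizes rest on assumed shifts, signal strength and numbers per arm, and on retraining that uses all later Arm 1 assessments.

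**What to change.** Add a scoring rule to section IV.F: each Arm 2 outcome is scored with an Arm 1 model trained only on Arm 1 outcomes from assessments earlier than that outcome. This means Arm 1 outcomes up to month 6 for the 9-month outcome, and up to month 9 for the 12-month outcome. Base any forecasting claim on these results. Report the fully retrained model beside them, labelled as validation in new individuals.

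Because the rule is tied to the date of the outcome, it works whether a quarter's watch data are paired with the survey that closes that quarter or with the one after it. In the second case only the 12-month outcome in Arm 2 can be scored.

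The cost is saving or refitting the earlier Arm 1 versions and one more scoring run. No further participants, data or procedures are needed. The downside is that the forward versions learn from fewer assessments, so their figures may be slightly less favourable.

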## **II. Background and Significance:**

Upwards of 40% of physicians have burnout. Physicians at the front lines of caring for patients with COVID-19 are at highest risk, and at least since 2011 burnout has been more prevalent among physicians than other US workers. Multiple systematic reviews and meta-analyses have concluded clinician burnout impacts quality of care in important ways. For example, studies of clinicians have found burnout is independently associated with medical error, medical malpractice suits, poor professionalism, absenteeism, low job performance, less favorable cost conscious attitudes, racial biases, lower competency, job dissatisfaction, patient dissatisfaction ratings across a variety of domains, and longer patient recovery times. Physicians with burnout are approximately twice as likely to quit their jobs and reduce clinical hours, resulting in a loss of productivity and access to care. At an organizational level burnout-attributable costs related to job turnover and reduced clinical hours among physicians alone are approximately \$7600 per physician each year with approximately \$4.6 billion in cost on a national scale. Additionally, studies have also found burnout to be independently associated with sleep impairments, alcohol abuse/dependence, suicidal ideation, and motor vehicle incidents. Physicians are at increased risk of suicide compared to the U.S. general population.

Unfortunately, burnout is underrecognized by those who suffer from it, and it typically goes undetected until physicians' performance or health deteriorates. There is a moral and business case to develop pragmatic ways to identify physicians at risk for burnout. In recognition of the broad impact of physician well-being on individuals, healthcare organizations, and society, The National Academy of Medicine's consensus study on clinician burnout (co-authored by PI [name]) "call(ed) upon leaders in health care organizations and health professions, educational institutions, as well as within the government and industry to prioritize, prevent and mitigate burnout and foster professional well-being for the overall health of individuals and the nation."

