**D. Description, Risks and Justification of Procedures and Data Collection Tools:**

We do not foresee any adverse consequences for study participants. They will be asked to complete surveys in addition to wearing Smartwatches and sharing resulting physiologic data. The surveys and physiologic data from Smartwatches will be confidential and private. Database for this study will be password-protected and accessible only by authorized (by the study PI) research staff. All study datasets will be deidentified in accordance with HIPAA guidelines. Therefore, each study participant will be assigned a unique study subject ID number. Data collected from smartwatches and surveys will be linked to each subject ID number. For purposes of achieving the

analytic aims described above, inputs will include subject ID number, subject sex, data collected from smartwatches, and scores on surveys. Subject names, addresses, telephone numbers, or any other data that could serve as identifiers will not be entered into the study databases used for data analysis.

In regards to electronic data, we will use MS Excel for maintaining a list of participants, device serial number and basic information (e.g., department). The quarterly surveys will be collected via Mayo Clinic's Survey Research Center (they will send surveys to participants at both sites), which stores data from Qualtrics. Finally, smartwatch data will be collected via FitaBase - a 3rd party data aggregator which will not collect any PHI.

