## B. QUALITY OF LIFE (LASA)

1. How would you describe your overall quality of life during the past week, including today (0 = As bad as it can be, 10 = As good as it can be)?

0      1      2      3      4      5      6      7      8      9      10

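### The only numeric benchmark for Aim 2, accuracy above 70%, has no comparator, so reaching it would not show that the watch data carry a signal

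*Protocol*

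**What the plan says.** Protocol IV.F gives the Aim 2 question as "To determine whether continuous physiological measures (measured from Smartwatches) contain a 'signal' that predicts physician well-being", and asks in which dimensions. Five survey scores are cut into binary labels: low well-being, burnout, low quality of life (QOL), high stress and high fatigue. Four cuts are fixed scores. Low QOL is relative, at least half an "SD below the mean", and the text does not say whose mean and SD, or at which wave. In the survey instrument QOL is a single item scored 0 to 10 in whole points ("How would you describe your overall quality of life during the past week, including today").

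The models are trained in Arm 1 to "predict risk of low well-being, burnout, low QOL, high stress, and high fatigue in the next quarter" and evaluated in Arm 2. On structure, IV.F says: "We will derive dynamics for these dimensions of well-being using dynamic Bayesian networks (DBN)". Section IV.D says that, for the analytic aims, "inputs will include subject ID number, subject sex, data collected from smartwatches, and scores on surveys".

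AUC, sensitivity and specificity are to be reported, and predictors ranked by importance, but no value is attached to any of these. The one number is "We aim to achieve predictive accuracies > 70" per cent. No no-information rate, reference model or with-versus-without-watch comparison is stated.

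**The concern.** Aim 2 asks about the watch data specifically. Raw accuracy can be high for two reasons unrelated to the watch: the label is uncommon (or very common), or people tend to give similar answers from one quarter to the next. A benchmark without a comparator cannot separate these from physiological signal. A result above 70% could then be reported as evidence that watches predict well-being when it shows only that last quarter's survey predicts this quarter's survey.

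**Working it through.** The protocol gives no derivation of 70%, so there is no figure to reproduce. The check is what accuracy is available with no watch data.

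**Inputs**
- Burnout prevalence: "Upwards of 40% of physicians have burnout" (Protocol II), so p = 0.40. This is the only prevalence in the document.
- Low QOL: half an SD below the mean. If scores are normal, p = Φ(−0.5) = 0.309.
- Prevalences of the other three labels, and quarter-to-quarter correlations: not given. The correlation r between consecutive scores is an assumption, shown from 0.4 to 0.7.

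**Route 1: majority class.** Accuracy = max(p, 1 − p).
- Burnout: 1 − 0.40 = 60.0%.
- Low QOL under normality: 1 − 0.309 = 69.1%.
- The rule exceeds 70% only if p < 0.30 or p > 0.70.

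**Route 2: repeat last quarter's label.** With stable prevalence, accuracy = 1 − 2(p − p11), where p11 is the probability of being positive in both quarters. For p11 the label is treated as a dichotomised bivariate normal score with correlation r. Example: p = 0.40 and r = 0.6 give p11 = 0.257, so accuracy = 1 − 2(0.400 − 0.257) ≈ 71.5%.

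| r (assumed) | p = 0.40 | p = 0.309 |
|---|---|---|
| 0.4 | 64.4% | 68.0% |
| 0.5 | 67.8% | 71.0% |
| 0.6 | 71.5% | 74.2% |
| 0.7 | 75.5% | 77.8% |

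In terms of the correlation φ between the binary labels, accuracy = 1 − 2p(1 − p)(1 − φ). It exceeds 70% when φ > 1 − 0.3/(2p(1 − p)):
- p = 0.40: φ > 1 − 0.3/0.48 = 0.375.
- p = 0.309: φ > 1 − 0.3/0.427 = 0.30.

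On the score scale the crossing lies at r of about 0.5 to 0.6.

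**The QOL cut.** Assume a normal score rounded to whole points, SD 1.8, and a cut recomputed by arm or wave.
- Mean 7.0: cut = 7.0 − 0.9 = 6.1, so scores of 6 or less are low. Prevalence = Φ((6.5 − 7.0)/1.8) = 39%; all-negative accuracy 61%.
- Mean 6.8: cut = 6.8 − 0.9 = 5.9, so scores of 5 or less are low. Prevalence = Φ((5.5 − 6.8)/1.8) = 24%; all-negative accuracy 76%.

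The mean falls by 0.2, yet the share labelled low drops by about 15 points. With the cut held at 6 it would rise to Φ((6.5 − 6.8)/1.8) = 43%. This example also shows that the 31% used above is a normal-theory value that a whole-point item need not reproduce.

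**The case against.** **The 70% is an aspiration, not a decision rule.** This stands. The wording is an aim, no conclusion depends on it, the hypotheses section presents the prediction work as exploratory, and the advertising form calls it a secondary purpose. It lowers the severity, but this is still the only number against which Aim 2 can be judged.

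**The other metrics already protect the reader.** This stands in part. An all-negative model would show AUC 0.5 and sensitivity 0. A model driven by earlier survey answers can have a good AUC and good sensitivity. Ranking predictors may hint at the source of the performance but does not measure what the watch adds.

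**IV.D describes a dataset, not a predictor list.** A fair caution: survey scores must be in the data because they are the outcomes. But IV.F models the dynamics of those same states, so earlier survey states are plausible predictors and nothing excludes them. A reader might infer that subject ID is also a planned predictor. The text does not support that, since the ID is there to link records.

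**Guessing does not beat 70%.** Correct where the document gives information: 60% for burnout and 69.1% for low QOL under normality. Nor does persistence pass at every correlation (67.8% at r = 0.5 and 40% prevalence).

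**Hypothesis 3.** A reader might infer that the comparison of burnout with fatigue, stress and QOL would be settled by prevalence. Nothing says that it will be judged on raw accuracy, and AUC is to be reported.

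**The analysis plan may add a reference model.** It may. The benchmark is nevertheless fixed in the protocol without one.

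**Conclusion.** The point holds at moderate severity. As written, accuracy above 70% does not answer the Aim 2 question, because survey persistence alone reaches it once the quarter-to-quarter score correlation is about 0.5 (31% prevalence) to 0.6 (40% prevalence). This rests on three assumptions: earlier survey scores enter the models, prevalence is stable between quarters, and the correlation is that high. The protocol permits the first and gives no figures for the other two. The claim is that the target can be met without watch data, not that it will be.

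Majority-class guessing is the lesser route. It passes only for labels with prevalence below 30% or above 70%, and the planned AUC and sensitivity would reveal it. The unspecified QOL cut adds a smaller problem. The size of its shift depends on where the mean minus half an SD falls relative to a whole number, and the mean and SD used here are assumed. The randomised Aim 1 comparison is unaffected.

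**What to change.** - For each of the five labels, state the Aim 2 benchmark as the gain in Arm 2 AUC of the model with watch data over a reference model using sex and the last survey score only. Give a 95% CI from a bootstrap that resamples participants, so that repeated surveys from one person stay together.
- Report accuracy only beside the no-information rate, max(p, 1 − p), for that label.
- Fix the low-QOL cut once, as a whole-number score, from the pooled baseline survey completed before randomisation. Apply it unchanged to both arms and all waves.

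The changes should be made before the models are evaluated in Arm 2. They need no new data: the cost is a few sentences of protocol and analysis-plan text and one reference model per label. The downside is a harder and less flattering benchmark.
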